## 3. ANALYSIS POPULATION

All patients from the above studies who received at least one dose of study drug will be included in the paediatric safety population.

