## 8.2 Clinical laboratory data

Clinical laboratory data (AST, ALT, total bilirubin, direct bilirubin, if available, alkaline phosphatase, serum creatinine, haemoglobin, platelet count, white blood count, neutrophils, lymphocytes, eosinophils) will be summarised by treatment group and time point, including changes from Day 0 (pre-dose) with the number of observations, mean, standard deviation, median, quartiles, minimum and maximum.

SI values will be used for summarisation.

To evaluate potential anemia, incidence rates of patients having a hemoglobin change from baseline:

$\geq 0$  g/L,  $-20 < 0$  g/L, or  $< -20$  g/L will be summarized for each time point.

Incidence rates of liver enzyme abnormalities will be summarized by time point and for the worst (highest) value based on the following event criteria (note that criteria are not mutually exclusive):

| Parameter             | Criterion                                                                                                    |
|-----------------------|--------------------------------------------------------------------------------------------------------------|
| ALT                   | $\leq 1.5$ ULN, $> 1.5$ ULN and $\leq 3 \times$ ULN
$> 3 \times$ ULN; $> 5 \times$ ULN; $> 10 \times$ ULN |
| AST                   | $\leq 1.5$ ULN, $> 1.5$ ULN and $\leq 3 \times$ ULN
$> 3 \times$ ULN; $> 5 \times$ ULN; $> 10 \times$ ULN |
| ALT or AST            | $> 3 \times$ ULN; $> 5 \times$ ULN; $> 10 \times$ ULN                                                        |
| Total bilirubin (TBL) | $> 1.5 \times$ ULN, $> 2 \times$ ULN, $> 3 \times$ ULN                                                       |
| ALT or AST & TBL      | ALT or AST $> 3 \times$ ULN & TBL $> 2 \times$ ULN (Hy's Law)                                                |

ULN=upper limit of normal range of the local laboratory.

For a combined criterion to be fulfilled all criteria have to be fulfilled at the same time point.

Shift tables of the above categories at Day 0 versus the worst post baseline value will be generated.

The following graphical displays of liver function test data will be generated:

Comparison between treatment groups and between first and subsequent dosing using scatter plots of the peak total bilirubin value versus the peak ALT/AST values (expressed relative to the upper limit of normal) from Day 3 until Day 28 and from Day 7 until Day 28 (E-Dish graphs).

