Scatter plots for ALT, total bilirubin showing individual data by day (y axis will present value, x-axis will present Day 0, 3, 7 and 28) – separately for treatment groups for all patients and for patients who had at least one re-treatment.

ALT classifications relative to the normal ranges, incidence rates of potential liver abnormalities and shifts of ALT categories will further be summarised by body weight category.

Potential differences between PA and AL of ALT and AST classifications relative to the normal ranges will be analysed using the Chi-square test and incidence rates of potential liver abnormalities using Fisher's exact test.

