|                              | TBIL >1.5 x ULN                                     |                                                        |                                                        |         |
|                              | TBIL >2 x ULN                                       |                                                        |                                                        |         |
|                              | TBIL >3 x ULN                                       |                                                        |                                                        |         |
|                              | Hy's law (ALT or AST >3 x ULN
and TBIL >2 x ULN) |                                                        |                                                        |         |
| Day 3                        |                                                     |                                                        |                                                        |         |
| Day 7                        | ...                                                 |                                                        |                                                        |         |
| Day 28                       | ...                                                 |                                                        |                                                        |         |
| Highest value post Day 0 ... |                                                     |                                                        |                                                        |         |

ULN = Upper limit of normal range

TBIL = total bilirubin

p-value from Fisher's exact test for the difference between PA and AL.

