**Table 2.7.4-19**      **Shift table of ALT categories from Day 0 pre dose to the worst post dose value, by treatment**  
**Paediatric safety population**  
**(Page 1 of n)**

| Treatment               |                | Number (%) of patients: Day 0 |            |                |              |               |            |
|-------------------------|----------------|-------------------------------|------------|----------------|--------------|---------------|------------|
|                         |                | Total                         | <1.5 x ULN | >1.5-<=3 x ULN | >3-<=5 x ULN | >5-<=10 x ULN | >10 x ULN  |
| Pyronaridine artesunate | Total          | xxx (100)                     | xxx (xx.x) | xxx (xx.x)     | xxx (xx.x)   | xxx (xx.x)    | xxx (xx.x) |
|                         | <1.5 x ULN     | xxx (xx.x)                    | xxx (xx.x) | xxx (xx.x)     | xxx (xx.x)   | xxx (xx.x)    | xxx (xx.x) |
|                         | >1.5-<=3 x ULN | xxx (xx.x)                    | xxx (xx.x) | xxx (xx.x)     | xxx (xx.x)   | xxx (xx.x)    | xxx (xx.x) |
|                         | >3-<=5 x ULN   | xxx (xx.x)                    | xxx (xx.x) | xxx (xx.x)     | xxx (xx.x)   | xxx (xx.x)    | xxx (xx.x) |
|                         | >5-<=10 x ULN  | xxx (xx.x)                    | xxx (xx.x) | xxx (xx.x)     | xxx (xx.x)   | xxx (xx.x)    | xxx (xx.x) |
|                         | >10 x ULN      | xxx (xx.x)                    | xxx (xx.x) | xxx (xx.x)     | xxx (xx.x)   | xxx (xx.x)    | xxx (xx.x) |
| Artemether lumefantrine | Total          | xxx (100)                     | xxx (xx.x) | xxx (xx.x)     | xxx (xx.x)   | xxx (xx.x)    | xxx (xx.x) |
|                         | <1.5 x ULN     | xxx (xx.x)                    | xxx (xx.x) | xxx (xx.x)     | xxx (xx.x)   | xxx (xx.x)    | xxx (xx.x) |
|                         | >1.5-<=3 x ULN | xxx (xx.x)                    | xxx (xx.x) | xxx (xx.x)     | xxx (xx.x)   | xxx (xx.x)    | xxx (xx.x) |
|                         | >3-<=5 x ULN   | xxx (xx.x)                    | xxx (xx.x) | xxx (xx.x)     | xxx (xx.x)   | xxx (xx.x)    | xxx (xx.x) |
|                         | >5-<=10 x ULN  | xxx (xx.x)                    | xxx (xx.x) | xxx (xx.x)     | xxx (xx.x)   | xxx (xx.x)    | xxx (xx.x) |
|                         | >10 x ULN      | xxx (xx.x)                    | xxx (xx.x) | xxx (xx.x)     | xxx (xx.x)   | xxx (xx.x)    | xxx (xx.x) |

ULN = upper limit of normal range

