Patients with a pre-dose and at least on post dose ALT value are included.

**Table 2.7.4-20**      **Shift table of AST categories from Day 0 pre dose to the worst post dose value, by treatment  
Paediatric safety population**

*Programming note: Same layout as Table 2.7.4-19 for AST*

**Table 2.7.4-21**      **Summary of haemoglobin values (g/L) by treatment and time point  
Paediatric safety population**

*Programming note: Same layout as Table 2.7.4-11 for haemoglobin*

**Table 2.7.4-22**      **Summary of platelet values (10\*\*3/mm\*\*3) by treatment and time point  
Paediatric safety population**

*Programming note: Same layout as Table 2.7.4-11 for platelets*

**Table 2.7.4-23**      **Summary of white blood cell count values (10\*\*3/mm\*\*3) by treatment and time point  
Paediatric safety population**

*Programming note: Same layout as Table 2.7.4-11 for WBC*

**Table 2.7.4-24**      **Summary of absolute neutrophils (10\*\*3/mm\*\*3) by treatment and time point  
Paediatric safety population**

*Programming note: Same layout as Table 2.7.4-11 for absolute neutrophils*

**Table 2.7.4-25**      **Summary of absolute lymphocytes (10\*\*3/mm\*\*3) by treatment and time point  
Paediatric safety population**

*Programming note: Same layout as Table 2.7.4-11 for absolute lymphocytes*

**Table 2.7.4-26**      **Summary of absolute eosinophils (10\*\*3/mm\*\*3) by treatment and time point  
Paediatric safety population**

*Programming note: Same layout as Table 2.7.4-11 for absolute eosinophils*

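### Post-Day 0 liver-event rates and their tests count children already above the limit at Day 0, and the bilirubin and Hy's Law shift tables that Section 8.2 implies have no shell

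*SAP*

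**What the plan says.** Section 8.2 defines liver events as threshold crossings: "Incidence rates of liver enzyme abnormalities will be summarized by time point and for the worst (highest) value based on the following event criteria". The criteria cover ALT, AST, ALT or AST, total bilirubin (above 1.5, 2 and 3 x ULN) and the combined Hy's Law criterion. Section 3 sets the population: "All patients from the above studies who received at least one dose of study drug will be included in the paediatric safety population".

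Table 2.7.4-18 uses one n / total layout for Day 0, Days 3, 7 and 28, and a last block, "Highest value post Day 0". Its footnote reads "p-value from Fisher's exact test for the difference between PA and AL". Table 2.7.4-35 repeats the layout by body weight category. On testing, Section 8.2 says that the ALT and AST classifications "will be analysed using the Chi-square test and incidence rates of potential liver abnormalities using Fisher's exact test". No baseline stratum or adjustment is named.

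Section 8.2 also says: "Shift tables of the above categories at Day 0 versus the worst post baseline value will be generated". The shift shells in Section 12 are Table 2.7.4-19 ("Shift table of ALT categories from Day 0 pre dose to the worst post dose value, by treatment"), Table 2.7.4-20 ("Shift table of AST categories from Day 0 pre dose to the worst post dose value") and Table 2.7.4-36 (ALT by weight category). None covers total bilirubin, ALT or AST combined, or Hy's Law.

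**The concern.** The Day 0 rows show that the plan allows for abnormal liver values before dosing. A child above a limit at Day 0 and still above it at Day 3 counts as an event in the Day 3 row and in the highest-value row, and enters the Fisher test there. The tested comparison thus mixes what was present before treatment with what arose after it.

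The shift tables are where the two would be told apart child by child, but they carry no test, and for bilirubin and Hy's Law they have no shell. Sections 9 and 10 refer to Section 12 for the list of outputs, so a programmer working from the shells would not produce them. At stake is how reliably the pooled comparison shows, or rules out, a hepatic difference between PA and AL.

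**Working it through.** **What the documents fix.** No text or footnote limits the numerator or denominator of the post-Day 0 rows by Day 0 status. The SAP does state such conditions where it wants them: the ALT shift table requires a pre-dose and a post-dose value, and the haemoglobin change table uses available observations. With all treated patients in the population, no restriction is the natural reading.

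**What the documents do not give.** There is no sample size, alpha, event rate or Day 0 prevalence, so there is no planned figure to reproduce. All inputs below are assumptions.

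**Formula.** Per arm, b is the share above the limit at Day 0, s the share of those still above it after dosing, and p the new-onset rate among the rest. The planned table shows q = b·s + (1−b)·p. With b and s equal in both arms, the risk difference is (1−b)(p_PA − p_AL), close to the true one, but the common term b·s pulls the ratio towards 1.

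**Equal Day 0 prevalence.** Assume 500 PA and 330 AL children and new onset of 4% v 1% (ratio 4.0, difference 3.0 points). For b = 5%, s = 0.5:
- PA: 0.05 × 0.5 + 0.95 × 0.04 = 6.30%
- AL: 0.05 × 0.5 + 0.95 × 0.01 = 3.45%
- Ratio 1.83; difference 2.85 points.

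Power is for Fisher's exact test at two-sided 0.05, summing the two binomial distributions over all tables with p < 0.05. New-onset denominators are 500(1−b) and 330(1−b). Simulating the same scenarios agrees within about two points.

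| b | s | Ratio shown | Power, all patients | Power, new onset |
|---|---|---|---|---|
| 0.5% | 0.5 | 3.4 | 70.0% | 74.9% |
| 1% | 0.1 | 3.7 | 72.5% | 74.4% |
| 1% | 0.5 | 3.0 | 65.4% | 74.4% |
| 2% | 0.5 | 2.5 | 57.3% | 74.0% |
| 5% | 0.1 | 3.0 | 62.9% | 72.2% |
| 5% | 0.5 | 1.8 | 41.5% | 72.2% |
| 10% | 0.5 | 1.5 | 27.2% | 69.3% |

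A second set of assumptions (800 PA, 400 AL, new onset 3% v 1%, full persistence, normal approximation) gives the same pattern. For b from 0.5% to 5%, the true ratio of 3.0 appears as 2.33 down to 1.32. Power is 50% down to 21%, against 59% to 57% on new-onset events. The difference stays at 1.99 to 1.90 points.

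**Unequal Day 0 prevalence, full persistence.** Section 1 lists SP-C-003-05 with PA patients only, so the arms need not match at baseline.
- No drug difference (2% v 2%), Day 0 prevalence 3% PA v 1% AL: 0.03 + 0.97 × 0.02 = 4.94% v 0.01 + 0.99 × 0.02 = 2.98%. The table shows a ratio of 1.66 where the truth is 1.0.
- New onset 3% v 1%, Day 0 prevalence 1% PA v 3% AL: 0.01 + 0.99 × 0.03 = 3.97% v 0.03 + 0.97 × 0.01 = 3.97%. The table shows 1.0 where the truth is 3.0.

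**The case against.** This is a descriptive pooled safety summary with no stated hypothesis, alpha or power. Showing all-patients threshold rates beside shift tables is a legitimate choice, and ALT and AST already have that pairing. This stands as a reason to keep the all-patients counts. It does not answer the point that every planned liver p-value ignores Day 0 status.

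A reader might infer that nothing in the plan separates new from pre-existing bilirubin abnormality. That goes too far. Section 8.2 commits to shift tables, Table 2.7.4-18 has Day 0 rows for bilirubin and Hy's Law, Table 2.7.4-13 summarises bilirubin changes from Day 0, and Figure 2.7.4-7 plots bilirubin over time, with individual data by day including Day 0 according to Section 8.2. None of these, however, gives a count of newly occurring events.

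The shift-table sentence could also be read narrowly, as meaning only the banded ALT and AST rows. Yet it follows a list that includes bilirubin and Hy's Law, so at the least the text needs to say which is meant.

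Finally, testing only new-onset events would lose worsening within a criterion: a child going from 3.1 to 4.9 x ULN would leave the tested row for above 3 x ULN. That stands, and argues for adding a column rather than replacing one.

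**Conclusion.** The point holds as a distortion of unknown size and direction. It rests on the natural reading of an undefined denominator.

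A reader might conclude that the plan necessarily dilutes a drug effect. The documents do not support that. Dilution of the ratio and loss of power need similar Day 0 prevalence in both arms and persisting abnormality. With a PA-only source in the pool, prevalence may differ, and the bias can then run either way.

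Nor can the size be fixed. Under the assumptions above, it is close to nothing where Day 0 abnormality is rare (0.5 to 1%) and mostly resolves, and large at 5 to 10% with half persisting. Prevalence will also differ by criterion, from bilirubin above 1.5 x ULN to Hy's Law.

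The disagreement between the shift-table sentence in Section 8.2 and the shells in Section 12 needs no assumptions beyond the plain reading of that sentence. The whole point is a worthwhile, inexpensive improvement rather than a fault that invalidates the analysis.

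**What to change.** 1. Define the denominator in Tables 2.7.4-18 and 2.7.4-35.
2. In both tables, add for the post-Day 0 rows a column of newly occurring events with its own Fisher p-value. The denominator is children at or below that criterion's limit at Day 0 with at least one post-dose value. For Hy's Law it is children not meeting the combined criterion at Day 0. Keep the all-patients counts beside it.
3. Add a total bilirubin shift shell, using bands that follow from the Section 8.2 limits (up to 1.5, above 1.5 to 2, above 2 to 3, above 3 x ULN).
4. Add a new-versus-pre-existing display for Hy's Law, showing which component was already raised at Day 0.
5. Word the shift-table sentence in Section 8.2 so that it names the parameters covered and matches Section 12.

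The cost is SAP wording, one column in two tables and two shells, all from data that the planned tables already use. Children with no Day 0 value leave the new-event denominator, and worsening within a criterion is seen only in the all-patients counts and shift tables. The extra p-values should be read as descriptive.

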## 8. SAFETY ANALYSIS

### 8.1 Adverse events

The following adverse event summaries will be generated by treatment group.

- An overview of the number and percentage of patients with
  - any adverse event
  - any serious adverse event
  - any severe or life-threatening adverse event
  - any adverse event considered to be related to study drug, whereby related will be defined as possible, probable, definite, or missing relationship, as assessed by the investigator. If the relationship to study medication is missing the worst case will be assumed, i.e. such AEs will also be considered study drug related.
  - any serious adverse event considered to be related to study drug
  - any adverse event leading to death.
- Number and percentage of patients with adverse events by MedDRA primary system organ class and preferred term by treatment group
- Number and percentage of patients with study drug related adverse events (defined as possible, probable, definite or missing relationship to study drug) by MedDRA primary system organ class and preferred term by treatment group
- Number and percentage of patients with serious adverse events by MedDRA primary system organ class and preferred term by treatment group

- Number and percentage of patients with adverse events by MedDRA primary system organ class, preferred term and maximal severity, by treatment group

Listings of all serious adverse events will be provided.

The overview of AEs, AEs by primary system organ class and preferred term, AEs considered to be drug related by primary system organ class and preferred term, serious AEs and serious AEs considered to be drug-related will further be summarized by body weight category and treatment.

Potential differences between PA and AL in AE incidence rates will be analysed using Fisher's exact test.

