**Table 2.7.4-13**      **Summary of total bilirubin values (umol/L) by treatment and time point**  
**Paediatric safety population**

*Programming note: Same layout as Table 2.7.4-11 for total bilirubin*

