**Table 2.7.4-14**      **Summary of alkaline phosphatase values (U/L) by treatment and time point**  
**Paediatric safety population**

*Programming note: Same layout as Table 2.7.4-11 for alkaline phosphatase*

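### The row labelled Hy's Law is a biochemical screen that can count haemolytic and cholestatic patterns, and no planned output lets a reader sort the counted children

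*SAP*

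**What the plan says.** - **The criterion.** The event table in SAP Section 8.2 ends with "ALT or AST $> 3 \times$ ULN & TBL $> 2 \times$ ULN (Hy's Law"). The shell of Table 2.7.4-18 repeats it as "Hy's law (ALT or AST >3 x ULN and TBIL >2 x ULN"), and Table 2.7.4-35 reuses that layout by body weight category.
- **Timing.** Section 8.2 adds: "For a combined criterion to be fulfilled all criteria have to be fulfilled at the same time point".
- **Testing.** Section 8.2 and the footnote to Table 2.7.4-18 compare these incidence rates between PA and AL with Fisher's exact test.
- **ALP and direct bilirubin.** Section 8.2 names both for descriptive summary: "total bilirubin, direct bilirubin, if available, alkaline phosphatase". ALP has a shell, Table 2.7.4-14 ("Summary of alkaline phosphatase values (U/L) by treatment and time point"), and total bilirubin has Table 2.7.4-13 ("Summary of total bilirubin values (umol/L) by treatment and time point"). Section 12 has no shell for direct bilirubin. Neither ALP nor direct bilirubin appears in any event criterion.
- **Listings.** Section 8.1 states: "Listings of all serious adverse events will be provided". The only listing shell, Listing 2.7.4-1, is for serious adverse events and has no laboratory columns.

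**The concern.** This is the only row in the plan that combines transaminase and bilirubin elevation, so it will be read as the most serious liver finding. The label carries no qualifier. The rule lets AST stand in for ALT and has no term that separates a cholestatic pattern (raised ALP) from a hepatocellular one, or indirect from direct bilirubin.

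The children have malaria, and the plan itself looks for anaemia through falls in haemoglobin. If red-cell breakdown raises both AST and indirect bilirubin in some of them, those children can meet the rule without liver injury. That mechanism is a general clinical assumption, not something the SAP states.

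At stake is how the row can be interpreted. A difference between PA and AL, or its absence, would rest on counts that may mix three patterns. A reader of the planned outputs would have no dependable way to say which pattern each counted child had.

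**Working it through.** The SAP states no count, rate or sample size on this point, so there is no figure to reproduce. The check applies the rule to assumed profiles and then goes through the planned outputs.

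**Step 1. Rules compared** (all values in multiples of ULN, at one time point)
- R0, the SAP rule: (ALT >3 or AST >3) and TBL >2.
- R1: ALT >3 and TBL >2.
- R2: R0 and ALP <2. The cut-off of 2 is an example only; the SAP gives none.

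**Step 2. Assumed profiles**

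| Profile | ALT | AST | ALP | TBL | R0 | R1 | R2 |
|---|---|---|---|---|---|---|---|
| (a) AST-driven, bilirubin mainly indirect | 1 | 3.5 | 1 | 2.5 | met | not met (1 ≤ 3) | met |
| (b) raised ALP | 3.5 | 3.5 | 4 | 3 | met | met | not met (4 ≥ 2) |
| (c) hepatocellular | 6 | 5 | 1 | 3 | met | met | met |

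R0 counts all three alike. R1 removes (a) only and R2 removes (b) only; requiring both leaves (c). Every child meeting R1 or R2 also meets R0, so the SAP row misses nobody whom the narrower rows would count. Neither R1 nor R2 uses direct bilirubin, so a child with raised ALT and mainly indirect bilirubin could be recognised only from individual values.

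**Step 3. Can the planned outputs separate (a), (b) and (c)?**
- *Single-enzyme rows in Table 2.7.4-18.* These count ALT and AST elevations separately, but do not show whether the same child also had TBL >2 × ULN.
- *E-DISH plots, Figures 2.7.4-1 to -4.* ALT and AST are plotted separately, which helps. But Section 8.2 plots peak against peak over Day 3 to 28 or Day 7 to 28, while the criterion requires the same time point. A child with ALT >3 on Day 3 only and TBL >2 on Day 7 only falls in the upper-right area without being a counted case. A child counted through AST alone on Day 3 whose ALT passes 3 on Day 7 falls there on the ALT plot too. Neither plot carries ALP or direct bilirubin.
- *Plots over time, Figures 2.7.4-5 to -7.* These show individual ALT, AST and total bilirubin values by day in separate figures. The text does not ask for points to be linked across figures. The figure mock-ups could not be seen, so point labels cannot be ruled out.
- *Table 2.7.4-14.* ALP mean, SD, quartiles, minimum and maximum by arm and day, not tied to any flagged child.
- *Table 2.7.4-27.* Categories of haemoglobin change by arm and day, likewise not linked.
- *Shift tables.* Section 8.2 announces these for its categories in general, but Section 12 has shells for ALT and AST only. For the combined criterion, the Day 0 row gives a group count, and no table shows whether a post-dose case already met it before dosing.
- *Listing 2.7.4-1.* Serious adverse events only, without laboratory values.

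No planned output assembles one counted child's values.

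**Step 4. Size.** The share of R0 cases that look like (a) or (b) is not given and cannot be derived from the SAP. Its range is 0% to 100%.

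**The case against.** The strongest case for the plan is that this is a screen and is presented as one. The text treats these rows as possible liver abnormalities, the definition is printed beside the label, and the row is tabulated at Day 0 as well as after dosing. Accepting AST makes the screen more sensitive, which is a defensible choice for safety. All of that stands, and it is why the row should be kept.

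A reader might infer that the plan reports haemolysis or cholestasis as hepatocellular drug injury. The SAP does not support that: nowhere does it attribute a counted case to the drug or to hepatocellular damage. A reader might also infer that a true signal would be missed. Step 2 shows that the row contains every child the narrower rows would count, so at most a contrast between arms is diluted.

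Nor is it right that a flagged child is visible only as a count, or that ALP is only averaged. There are individual-value plots, and the ALP summary includes quartiles and extremes. What remains is that none of this is linked within a child.

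Two further points stand in part. The SAP covers a pooled analysis of three studies, and patient-level listings or narratives may exist in the individual study reports, which are not at hand. They would help, but would not make the pooled row interpretable on its own. And direct bilirubin is to be summarised only if available. That may explain sparse data, but a conditional summary still needs a shell, because Sections 9 and 10 refer to Section 12 for all outputs.

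**Conclusion.** The point holds as a matter of labelling and missing case-level output, not as an error in the screen. Followed as written, the plan can count haemolytic, cholestatic and hepatocellular patterns together under an unqualified Hy's Law label, compare that count between PA and AL, and leave the reader unable to sort the cases reliably. The missing direct bilirubin shell is a separate, minor mismatch between Section 8.2 and Section 12.

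The size is unknown: the affected share of counted children may be anything from 0% to 100%. The conclusion rests on the wording of the rule and the list of outputs, both of which can be checked. It also assumes that such patterns can occur in these children, which the SAP neither states nor excludes. This is a worthwhile, low-cost improvement.

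**What to change.** 1. Keep the combined row in Section 8.2 and Tables 2.7.4-18 and 2.7.4-35, but relabel it *potential Hy's Law (biochemical criterion)*.
2. Add two supportive rows to both tables: ALT >3 × ULN with TBL >2 × ULN, and the combined criterion without raised ALP. The sponsor should prespecify the ALP cut-off; <2 × ULN is only an example. The same-time-point rule should apply to both rows.
3. Add a listing of every child who meets the combined criterion, showing ALT, AST, ALP, total and direct bilirubin and haemoglobin by day, including Day 0.
4. Add a direct bilirubin summary shell in the layout of Table 2.7.4-11, to match Section 8.2.

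The cost is some SAP wording, two table rows, one listing and one summary table, all from analytes that Section 8.2 already names. The drawback is that ALP or direct bilirubin will be missing for some children. They should be shown as not classifiable rather than dropped or assigned to a pattern.

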## 1. INTRODUCTION

This analysis plan describes the ISS analyses planned for the Pyramax paediatric (granule) formulation submission to EMA.

For the analysis of paediatric safety data the safety data of the following studies will be pooled:

- SP-C-003-05, Cohort D, patients treated with the PA granule formulation weighing <20 kg
- SP-C-007-07 (both PA and AL) weighing <20 kg
- WANECAM paediatric patients (weighing <20 kg) from the corresponding sub study analysis, treatment episode 1 only.

All analyses will be performed by DATAMAP GmbH, Freiburg, Germany using SAS®, Version 9.3 in a UNIX environment.

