### Study days

Study days will be calculated as actual date minus date of first study drug intake, i.e. the day of first study drug intake will be defined as Day 0.

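### Section 8.2 promises liver plots on subsequent dosing and re-treated patients, but Section 1 identifies no source of data after re-treatment

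*SAP*

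**What the plan says.** SAP Section 1 defines the pool by three entries. One takes, from Cohort D of SP-C-003-05, those below 20 kg who were given PA granules. Another takes those below 20 kg in either arm of SP-C-007-07. The remaining entry reads "WANECAM paediatric patients (weighing <20 kg) from the corresponding sub study analysis, treatment episode 1 only".

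SAP Section 8.2 then lists the graphical displays of liver function tests. The E-DISH item is a "Comparison between treatment groups and between first and subsequent dosing using scatter plots of the peak total bilirubin value" against peak ALT/AST, both relative to the upper limit of normal, over Day 3 to Day 28 and Day 7 to Day 28. The next item is a set of scatter plots of individual ALT and total bilirubin values at Days 0, 3, 7 and 28, drawn "separately for treatment groups for all patients and for patients who had at least one re-treatment".

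Under Study days in SAP Section 2, "the day of first study drug intake will be defined as Day 0". Under Baseline in the same section, the reference value is the last one taken before study drug was first given. Neither definition provides for a later course.

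**The concern.** The two displays in Section 8.2 need laboratory values taken after a second or later course. WANECAM is the only pooled study for which the plan mentions treatment episodes, and Section 1 admits only its first.

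Liver tests are the most detailed laboratory topic in this plan, and the plan itself raises the question of re-dosing. If the programmers follow Section 1, one promised contrast has nothing on its second side. The other plot can still be drawn if re-treated children can be identified, but it would hold first-episode values under a heading about re-treated patients. A reader of a regulatory submission could take that plot as evidence about re-dosing, although WANECAM supplies no such evidence to it.

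**Working it through.** The plan gives no figure to reproduce and no sample-size arithmetic applies. The check sets the data scope beside the displays and asks whether any reading reconciles them.

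**1. Scope against displays**

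| Place in the SAP | What it fixes | Values after re-treatment? |
|---|---|---|
| Section 1, WANECAM | First treatment episode only | Excluded |
| Section 1, SP-C-003-05 Cohort D | Granule-formulation PA patients below 20 kg | None described; no episode limit stated |
| Section 1, SP-C-007-07 | PA and AL patients below 20 kg | None described; no episode limit stated |
| Section 8.2, E-DISH | First against subsequent dosing | Required |
| Section 8.2, plots over time | Subset with at least one re-treatment | Required, if the plot is to inform on re-treatment |

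**2. Could subsequent dosing mean later doses of the same course?** Section 7 counts vomiting over three PA doses and six AL doses. The shell of Table 2.7.4-3 allows one PA dose and two AL doses on Day 0. If that daily pattern continues, PA takes 3/1 = 3 days and AL takes 6/2 = 3 days, that is Days 0 to 2. Both E-DISH windows (from Day 3 and from Day 7) would then open after the last dose. In any case, one peak per patient over such a window cannot be divided among the doses of one course. The companion plot speaks of re-treatment, which points to a new course. This reading fails.

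**3. Could the first-episode limit be loose wording?** Other parts of the plan agree with it. Baseline and Day 0 refer to the first intake. A footnote to Table 2.7.4-1 judges completion on the first episode; it names SP-C-013-11, a number that Section 1 does not list and that is presumably WANECAM.

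**4. What would happen if later episodes were admitted without other changes?** Let a second course start *k* days after the first. With Day 0 fixed at the first intake:

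- its Day 3 sample has study day *k* + 3, beyond Day 28 when *k* > 25;
- its Day 7 sample has study day *k* + 7, beyond Day 28 when *k* > 21;
- its Day 28 sample has study day *k* + 28, beyond Day 28 for every *k* > 0.

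Values from a later course would therefore drop out of the windows or, for small *k*, mix with those of the first course. The displays need an episode-specific Day 0 as well as the data.

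**5. Figure shells.** The titles of Figures 2.7.4-1 to 2.7.4-7 name the laboratory test and, for the first four, the starting day. None mentions an episode or a re-treated subset. The layouts of Figures 2.7.4-1 and 2.7.4-5, on which the others are modelled, are not shown in the text at hand.

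**The case against.** The best case on the other side accepts the mismatch but limits what follows from it.

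- **Figure layouts.** A reader might infer that the shells contain no comparison of first with subsequent dosing. The documents do not support that: the two master layouts are not visible, so panels or symbols by episode cannot be ruled out. Only the silence of the titles can be cited. Such panels would still lack WANECAM data from later episodes.
- **No re-treatment data anywhere in the pool.** This is certain for WANECAM only. The other two studies carry no episode limit. That they had no re-treatment fits their description, but the plan does not say so.
- **A falsely reassuring result.** A reader might infer that the output would look favourable by construction, because children who went on to another course are a selected group. The plan gives no re-treatment criteria, so no direction of bias can be asserted. For the E-DISH contrast, a blank second side would be noticed. The re-treated plot could be drawn only if a re-treatment flag is carried into the first-episode data, which the plan does not mention.
- **Weight.** These are descriptive plots. No incidence table, Hy's law count, shift table, Fisher test or chi-square test rests on them, and the between-treatment half of the E-DISH comparison remains feasible.

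All four limits stand. None removes the conflict: nothing else in the plan supplies the missing data or withdraws the displays.

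**Conclusion.** The point holds. Section 8.2 commits to two displays that the data scope in Section 1 cannot support. The subsequent-dosing side of the E-DISH comparison has no identified data source, and the re-treated-patient plot could show only first-episode WANECAM values. Those values cannot inform liver safety on re-dosing, favourably or unfavourably. This is a contradiction within the plan, not detail left to another document.

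The size is two descriptive displays, with a WANECAM contribution of zero values from later episodes. The wider conclusion, that the pool has no such values at all, assumes no re-treatment in SP-C-003-05 Cohort D or SP-C-007-07. If there was any, the plan still lacks a baseline and a Day 0 for it.

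A reader might go further and conclude that liver safety on re-dosing cannot be shown for this product in children. The SAP does not support that. The limit applies to this pooled analysis. The WANECAM sub-study analysis named in Section 1 is not at hand and may or may not cover later episodes.

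**What to change.** Reconcile SAP Section 1 with Section 8.2 before programming, by one of two routes.

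**(a) Supply the data.** Keep the first episode for all pooled tables. Add WANECAM episodes 2 and later as a separate data set used only for these displays, with Day 0 and baseline defined for each episode, and figures whose titles name the episode or the re-treated subset. The cost is small: extra data definitions, figure shells and programming, with no new patients or procedures. It depends on the later-episode laboratory data being available at time points that suit the plots.

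**(b) Withdraw the displays.** Delete the comparison of first with subsequent dosing and the re-treated-patient plots. State that this pooled analysis supports no conclusion on re-dosing, and refer to the WANECAM sub-study analysis if it covers later episodes. The cost is wording only.

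Either route resolves the contradiction. Additional tables by episode are not needed, since the plan does not promise any.
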